#### Secondary outcomes

Secondary outcomes will also be analyzed using a Bayesian approach, similar to the primary outcome but using the appropriate model for the outcome distribution.

### Interim analyses {21b}

We will conduct two interim analyses, after 40 and 80 randomised participants, and a final analysis after the expected maximum of 120 randomised participants. The trial will be stopped early if the probability that the 90-day survival odds ratio (OR) falls below 1 (i.e. REBOA is harmful) at the first or second interim analysis is 90% or greater. More formally, our Bayesian futility criterion at each stage is *P* (*δ <* 0 | *y*) ≥ 0*.*9 where *δ* is the log OR and *y* is the observed data. REBOA will be declared “successful” if the probability that the 90-day survival OR exceeds 1 at the final analysis is 95% or greater, so our Bayesian success criterion is defined as *P* (*δ >* 0 | *y*) ≥ 0*.*95. Our calculations are based on an estimated control group (standard major trauma centre treatment alone) 90-day survival rate of 66.5% [35].

### Methods for additional analysis (e.g. subgroup analyses) {20b}

We do not plan to conduct additional or subgroup analyses.

### Methods in analysis to handle protocol non-adherence and any statistical methods to handle missing data {20c}

We do not anticipate missing data for the primary outcome. The primary analysis will be by intention to treat.

### Plans to give access to the full protocol, participant-level data, and statistical code {31c}

Formal requests for access to anonymised study data and/or to the statistical code will be considered on a case-by-case basis by the trial management group.

## Oversight and monitoring

### Composition of the coordinating centre and trial steering committee {5d}

#### Coordinating centre

The study is led by the Centre for Healthcare Randomised Trials in the Health Services Research Unit at the University of Aberdeen. The Project Management Group consists of the two co-Chief Investigators, a Trial Manager, a Senior Trial Manager, and a Data Coordinator.

#### Trial steering committee

The trial is overseen by an independent Trial Steering Committee (TSC), which includes two patient/public representatives. The TSC meets at least annually. The TSC adheres to a charter which is available upon request to the lead author.

### Composition of the data monitoring committee, its role, and reporting structure {21a}

The trial is monitored by an independent data monitoring committee (DMC). The DMC meets at least annually and reports to the trial steering committee. The DMC adheres to a charter which is available upon request to the lead author.

### Adverse event reporting and harms {22}

As this study is recruiting in trauma patients with life-threatening injuries, it is expected that many of the patients will experience events that are the consequence of the patient’s life-threatening injuries, resulting critical illness, and treatment. All adverse events/device effects occurring between randomisation and discharge are recorded in the appropriate case report form and closely monitored by the oversight committees.

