## Methods: participants, interventions, and outcomes

### Study setting {9}

The trial is being conducted in 16 major trauma centres in England, listed in Fig. 4. Major trauma centres are specialist, tertiary centres designated to provide definitive care for seriously injured patients. Screening, recruitment, and baseline data collection therefore take place in emergency departments. Patients are followed up to discharge from acute care, and virtually (by data linkage) after discharge.

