### Outcomes {12}

#### Primary clinical outcome measure

The primary clinical outcome is 90-day mortality (defined as death within 90 days of injury, before or after discharge from hospital). This outcome is intended to capture any late harmful effects of REBOA.

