#### NHS Digital Data

In addition to drawing on TARN data, the trial also links to NHS England’s Hospital Episode Statistics (HES) data to obtain information on hospital resource use and to Office of National Statistics (ONS) data for medium-term (6-month) mortality.

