#### EQ-5D-5L

Following the first linkage run, it became clear that the EQ-5D-5L results collected by the third-party provider contracted by TARN were incomplete. We therefore asked sites to collect EQ-5D-5L data prior to discharge, and subsequently at approximately 6 months by telephone.

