#### Expected complications

Death and a number of expected complications (including some which result in life-threatening illness, permanent impairment of structure or function, additional medical or surgical intervention, or prolonged hospital stay) are pre-specified outcomes and will therefore not be reported as serious adverse events (SAEs) or serious device adverse events (SADEs). Only unexpected SAEs/SADEs will be reported to the sponsor.

The following adverse events can be expected to occur as a result of using REBOA. Access-related adverse device effects (ADEs): external haemorrhage at insertion site requiring treatment other than simple pressure, pseudoaneurysm, arteriovenous fistula, dissection of artery, extremity ischaemia, stenosis of artery, distal embolism, air embolism, infection requiring surgical intervention, need for patch angioplasty (surgical repair), need for arterial bypass, and need for amputation. Other adverse device effects (ADEs) are balloon rupture, aortic rupture, and side branch cannulation.

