#### Follow-up procedures

All AEs/ADEs assessed by the PI or designee as possibly, probably, or definitely related to the device and all SAEs/SADEs that occur during this time will be followed until they are resolved or are clearly determined to be due to a patient’s stable or chronic condition or intercurrent illness(es). The CRF should be updated with the date and time of resolution or confirmation that the event is due to the patient’s illness as soon as this information becomes available.

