The pragmatic design does not, however, mandate specific actions, during the patient’s initial resuscitation, or subsequently. Given the heterogeneity of trauma patients and their injuries, this would be difficult to implement. In addition, the relatively small size of the trial, and the resulting credible intervals, may result in findings which are difficult to interpret. Furthermore, the choice of primary outcome (mortality at 90 days), which is intended to capture possible late detrimental effects of the technique, was made prior to research becoming available which suggests that haemorrhage control interventions should be evaluated with early mortality time points [34, 44, 45]. However, these have been included as secondary outcomes.

In conclusion, the UK-REBOA trial is a randomised, controlled, pragmatic trial that will provide the most definitive comparative data to date on the effectiveness of the procedure in reducing mortality in exsanguinating trauma patients.

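### Adverse events are recorded only up to discharge, so non-fatal complications that start later are not systematically collected as harms in either arm, and the observation window varies with length of stay

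*Protocol article*

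**What the plan says.** The opening paragraph of Adverse event reporting and harms {22} sets the recording period: "All adverse events/device effects occurring between randomisation and discharge are recorded in the appropriate case report form". Under Follow-up procedures, device-related events and all serious events "that occur during this time will be followed until they are resolved or are clearly determined to be due to" the patient's underlying condition or another illness. The only period that the article defines for adverse events is randomisation to discharge.

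Expected complications lists access-related device effects, among them "pseudoaneurysm, arteriovenous fistula, dissection of artery, extremity ischaemia, stenosis of artery, distal embolism". The two sections that follow list complications of open aortic occlusion and complications common to both treatments. Listed complications are exempt from serious adverse event reporting.

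Study setting {9} describes follow-up in two parts: "Patients are followed up to discharge from acute care, and virtually (by data linkage) after discharge". Under NHS Digital Data, the trial links to "Hospital Episode Statistics (HES) data to obtain information on hospital resource use", and to national death records for mortality to 6 months. Sites were also asked to "collect EQ-5D-5L data prior to discharge, and subsequently at approximately 6 months by telephone".

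Late harm is mentioned twice. Of 90-day mortality, the Outcomes section says: "This outcome is intended to capture any late harmful effects of REBOA". The Discussion repeats the reasoning for the same endpoint, "which is intended to capture possible late detrimental effects of the technique".

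**The concern.** Some listed complications, such as a narrowed artery, a false aneurysm or an infection that needs surgery, could plausibly first come to light after the patient has gone home. The article does not say when they appear. If they appear late, the case report form has already closed, and the harms table will not contain them.

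The window also ends at a date that treatment can influence. A patient who stays longer is watched longer. If REBOA changes length of stay, in either direction, the arms are compared over different amounts of time, and a difference or a lack of difference in complication counts is harder to read. In a trial of 120 patients a handful of events can change that table.

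**Working it through.** The plan states no figure on this point, so there is nothing to reproduce. The check is of the text, followed by an illustration of scale.

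**Text check: is there any route for a non-fatal event with first onset after discharge?**

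1. Case report form: closes at discharge.
2. Follow-up to resolution: continues past discharge, but only for events that arose in the recording period. Ischaemia noted in hospital and treated by amputation later is covered. A false aneurysm that first appears at home is not.
3. Serious event reporting: that section states no window of its own, but the listed complications are exempt from it, so it is no route for them.
4. Outcome lists: the clinical outcomes named in the article are mortality at several times, stay, blood use and haemorrhage control procedures. No non-fatal complication is named.
5. HES linkage: would probably show a readmission or repair, but is assigned to resource use.
6. Telephone contact at about 6 months: assigned to EQ-5D-5L. Lasting harm might lower the score, but the complication would not be identified.

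Routes 1 to 4 do not collect such an event. Routes 5 and 6 may hold traces of it, but are not designated to measure harm.

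**Unequal observation.** Suppose two patients each develop the same complication on day 45. One was discharged on day 20 and the other is still in hospital. Only the second is counted. If survivors stayed 20 to 40 days (an assumption; the article gives no length of stay), then (90 − 40)/90 = 56% to (90 − 20)/90 = 78% of a 90-day period would lie outside adverse-event recording. That is a share of days, not of events.

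**Scale.** Inputs from the article: 120 patients, 1:1 allocation, assumed control survival at 90 days of 66.5%. Survivors: 120 × 0.665 = 79.8, or 60 × 0.665 = 39.9 per arm, if REBOA survival equals the control assumption. For an assumed late-event rate p among n survivors, the expected number is n × p and the chance of at least one is 1 − (1 − p)^n. The row n = 30 is a sensitivity case, since survival in the REBOA arm may differ and the protocol lets clinicians withhold the balloon in that arm.

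| n | p = 1% | p = 2% | p = 5% | p = 10% |
|---|---|---|---|---|
| 40, expected | 0.4 | 0.8 | 2.0 | 4.0 |
| 40, at least one | 33.1% | 55.4% | 87.1% | 98.5% |
| 30, expected | 0.3 | 0.6 | 1.5 | 3.0 |
| 30, at least one | 26.0% | 45.5% | 78.5% | 95.8% |

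The rates are assumptions. The article offers nothing to choose between them.

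**The case against.** **The plan contradicts its own late-harm aim.** A reader might infer this, but the text does not support it. In both places the late-harm statement describes 90-day mortality, which is counted before or after discharge. Neither promises late capture of non-fatal events.

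**Only death is captured after discharge.** A reader might infer this too, and it is wrong. HES records, 6-month costs and EQ-5D-5L are also collected, so a patient readmitted on day 45 for a vascular repair should appear as a hospital episode. What is missing is its designation as a harm.

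**The loss falls mainly on the REBOA arm.** This is not shown. Open aortic occlusion has its own list of complications, a third list is common to both treatments, and a patient allocated to REBOA who receives no balloon may have no access injury. The direction of any imbalance is unknown.

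**The window is an openly stated, pragmatic choice, and details may stand elsewhere.** This has weight. The data strategy is meant to limit burden, the schedule of assessments has 90-day and 6-month points in a figure that is not shown, and the full protocol may say more. Silence on a HES code list would be no finding in itself. But the article does not merely omit the window: it states one that ends at discharge, and assigns HES to another purpose. That part of the point stands.

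**Conclusion.** The point holds in a limited form. Recording of new adverse events ends at discharge, nothing in the article extends it, and the length of observation depends on a post-randomisation outcome. Non-fatal complications with first onset after discharge are therefore not systematically collected as harms in either arm, and complication counts by arm need not cover equal time.

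The size cannot be fixed. Under the assumptions above it runs from less than one expected event to about four per arm. The lower end would hardly matter; the upper end would be visible in a safety table with 60 patients per arm. The primary analysis and the stopping rules are unaffected, since they rest on mortality. This is an inexpensive improvement worth making, not an error that undermines the trial.

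**What to change.** Keep site collection of adverse events to discharge. Before the final analysis, pre-specify a supplementary harms analysis that:

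- identifies the complications in the three expected-event lists (REBOA, open aortic occlusion, common to both) from linked HES records, with a code list fixed in advance;
- uses one fixed window from randomisation in both arms, either 90 days, close to the primary outcome, or 6 months, matching the within-trial economic analysis;
- reports results by randomised arm for all linked patients, with the number who could not be linked, and shows deaths alongside, since death also shortens the time at risk;
- stands next to the site-reported events and is not added to them, so that in-hospital events are not counted twice.

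Because it uses records already planned for linkage, it can be applied to linked patients enrolled since recruitment began.

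The costs are a code list and some analysis time. HES coding is less specific than site reporting. It covers only patients who can be linked and events that lead to hospital contact, and the stated purpose of the linkage may need to be extended. The report should state these limits.

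A complications question in the 6-month call is optional. Recruitment started on 1 January 2018 and was timetabled to end in June 2022, and the current protocol version is dated 25 November 2021. About 47 of 54 recruitment months (87%) had therefore passed, and a new question would reach only the later patients and give uneven ascertainment.

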#### Expected complications

Death and a number of expected complications (including some which result in life-threatening illness, permanent impairment of structure or function, additional medical or surgical intervention, or prolonged hospital stay) are pre-specified outcomes and will therefore not be reported as serious adverse events (SAEs) or serious device adverse events (SADEs). Only unexpected SAEs/SADEs will be reported to the sponsor.

The following adverse events can be expected to occur as a result of using REBOA. Access-related adverse device effects (ADEs): external haemorrhage at insertion site requiring treatment other than simple pressure, pseudoaneurysm, arteriovenous fistula, dissection of artery, extremity ischaemia, stenosis of artery, distal embolism, air embolism, infection requiring surgical intervention, need for patch angioplasty (surgical repair), need for arterial bypass, and need for amputation. Other adverse device effects (ADEs) are balloon rupture, aortic rupture, and side branch cannulation.

#### Adverse events related to standard treatment

The following adverse events can be expected to occur as a result of standard aortic occlusion, by means of a thoracotomy or laparotomy. Adverse events (AEs) related to external thoracic aortic occlusion are descending thoracic aortic injury, lung injury/bronchopleural fistula, cardiac injury, oesophageal injury, empyema, wound infection requiring surgical intervention, sternal non-union, rib fractures, extremity ischaemia, distal embolism, infection requiring antibiotics only, and infection requiring surgical intervention. Adverse events (AEs) related to external abdominal aortic occlusion are abdominal aortic injury, wound infection requiring surgical intervention, extremity ischaemia, distal embolism, infection requiring antibiotics only, and infection requiring surgical intervention.

#### Adverse events common to both treatments

Adverse events (AEs) related to impaired organ perfusion are acute kidney injury requiring renal replacement therapy, mesenteric ischaemia requiring surgical intervention, paraplegia (permanent), paraplegia (temporary), acute respiratory distress syndrome, stroke (embolic or hypoperfusion-related), and multi-organ failure.

#### Adverse event/device effect reporting

The principal investigator (PI) at each site or their delegated investigator is responsible for recording and reporting of AEs/ADEs observed during the study period. The PI must assess severity, seriousness, causality, and expectedness for any AEs/ADEs in keeping with regulatory requirements. The investigator should attempt, if possible, to establish a diagnosis based on the participant’s signs and symptoms. When a diagnosis for the reported signs or symptoms is known, the investigator should report the diagnosis as the AE/ADE, rather than reporting the individual symptoms.

#### Serious adverse event/device effect reporting

All events meeting the definition of a serious adverse event (SAE) or serious adverse device effect (SADE) will be entered onto the Serious Adverse Event/Serious Adverse Device Event reporting form and submitted to CHaRT within 24 h of the investigator becoming aware of the event. The PI at the site should not wait until all information about the event is available before notifying CHaRT of an SAE/SADE. Information not available at the time of the initial report must be documented on a follow-up SAE/SADE Form. Follow-up information should be sought and submitted as it becomes available. The follow-up information should describe whether the event has resolved or persists, if and how it was treated, and whether the patient continues on the study or has been withdrawn from treatment. Once received, seriousness, causality, and expectedness will be confirmed by the Chief Investigator (or delegated clinical lead). Unanticipated serious adverse device effects (USADE): SAEs that are deemed to be related to the study device or any of the research procedures and are unanticipated will be notified to the sponsor and Research Ethics Committee (REC) within 15 days of CHaRT becoming aware of the event.

#### Grading of severity of adverse events

The PI or designee will assess the severity for each AE using the following standard criteria. (1) Mild: The adverse event/device effect does not interfere with the participant’s daily routine and does not require intervention; it causes slight discomfort. (2) Moderate: The adverse event/device effect interferes with some aspects of the participant’s routine, or requires intervention, but is not damaging to health; it causes moderate discomfort. (3) Severe: The adverse event/device effect results in alteration, discomfort, or disability which is clearly damaging to health. (4) Life threatening: An adverse event/device effect that has life threatening consequences; urgent intervention indicated. (5) Fatal: An adverse event/device effect that results in death.

#### Assessment of seriousness

The PI or designee should make an assessment of seriousness. As stated above, death and a number of expected complications (including some which result in life-threatening illness, permanent impairment of structure or function, additional medical or surgical intervention, or prolonged hospital stay) are pre-specified outcomes and will therefore not be reported as SAEs/SADEs.

#### Assessment of causality

The PI or designee should make an assessment of the causality (i.e. relationship to trial device) for each event. Events which are possibly, probably, or definitely related to the device are reported as related. This will be determined as follows: (1) Definitely: There is clear evidence to suggest a causal relationship, and other possible contributing factors can be ruled out. (2) Probably: There is evidence to suggest a causal relationship, and the influence of other factors is unlikely. (3) Possibly: There is some evidence to suggest a causal relationship (e.g. the event occurred within a reasonable time after using the device). However, the influence of other factors may have contributed to the event (e.g. the patient’s clinical condition, other concomitant events). (4) Unlikely: There is little evidence to suggest there is a causal relationship (e.g. the event did not occur within a reasonable time after administration of the trial medication). There is another reasonable explanation for the event (e.g. the patient’s clinical condition, other concomitant treatments). (5) Not related: There is no evidence of any causal relationship. (6) Not assessable: Unable to assess on information available.

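### Events rated 'Not assessable' fall outside the related group, so unless re-rated they miss the 15-day notification and, if non-serious, follow-up to resolution

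*Protocol article*

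**What the plan says.** The Protocol article, under Assessment of causality, has the site grade each event as definitely, probably, possibly, unlikely, not related or not assessable. It then fixes which grades count: "Events which are possibly, probably, or definitely related to the device are reported as related". The last category is defined as "6) Not assessable: Unable to assess on information available", with no statement of how such an event is handled.

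Two other sections depend on this cut:

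- Serious adverse event/device effect reporting sets a 15-day notification to the sponsor and the ethics committee. Its trigger is that "SAEs that are deemed to be related to the study device or any of the research procedures and are unanticipated will be notified". The clock starts when the trials unit learns of the event.
- Follow-up procedures names the same three related grades, plus all serious events, as those to be followed until resolved or explained.

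The serious-event section also asks for early reports: "The PI at the site should not wait until all information about the event is available before notifying CHaRT".

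**The concern.** The related group is a closed list of three grades, and the same list appears in two sections. An event whose cause cannot be judged on the information at hand is left out of it. The document therefore sets the cut itself, and as written the cut works against detection: lack of information has the same reporting effect as a judgement that the device was not involved.

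The setting makes early uncertainty plausible. Patients are incapacitated at enrolment (Who will take informed consent?). Adverse event reporting and harms expects many events to arise from the injuries themselves, and first reports are to be sent before the information is complete. At stake are the one event-level route to the ethics committee that the article ties to relatedness, and the follow-up that might supply the missing information on cause.

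**Working it through.** No figure in the document bears on this point, so there is nothing to recompute. The check follows an event rated *Not assessable* through each route that the article describes.

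| Route (section) | Condition for entry | Event rated *Not assessable* |
|---|---|---|
| Related group (Assessment of causality) | One of three named grades | Left out |
| 15-day notification to sponsor and ethics committee (Serious adverse event/device effect reporting) | Serious, deemed related, unanticipated | Not triggered unless re-rated |
| Follow-up to resolution (Follow-up procedures) | One of the three grades, or any serious event | Kept if serious; lost if non-serious |
| 24-hour report to the trials unit (Serious adverse event/device effect reporting) | Meets the definition of a serious event | Still made |
| Report to sponsor (Expected complications) | Serious and unexpected | Still made |
| Case report form record and committee oversight (Adverse event reporting and harms) | Any event from randomisation to discharge | Still made |

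The texts behind the unaffected rows carry no causality condition. For the 24-hour report: "All events meeting the definition of a serious adverse event (SAE) or serious adverse device effect (SADE) will be entered onto" the reporting form. For the sponsor: "Only unexpected SAEs/SADEs will be reported to the sponsor"; that sentence states no time limit and does not mention the ethics committee.

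Next, whether later steps restore the two lost routes.

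1. *Central confirmation.* The article says "Once received, seriousness, causality, and expectedness will be confirmed by the Chief Investigator (or delegated clinical lead". This can turn a *Not assessable* rating into a related one. However, it covers only submitted serious-event forms, follows receipt of a report that may be incomplete, and comes with no other grading scale. It offers a chance of re-rating but sets no rule for an event that remains unassessable.
2. *Follow-up information.* It is to be sought and sent as it becomes available. Its listed content is resolution, treatment given and whether the patient continues. Re-rating of causality is not mentioned.
3. *The clock.* Because the 15 days run from awareness of the event and not from a change of rating, a re-rating after day 15 comes too late for the stated limit.
4. *Non-serious events.* They do not pass through central confirmation, and a *Not assessable* rating takes them out of follow-up. Nothing described prompts a second look at their cause.

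Last, listed complications such as extremity ischaemia, distal embolism and acute kidney injury needing renal replacement. Expected complications and Assessment of seriousness keep these out of serious-event reporting because they are pre-specified outcomes. Their causality grade therefore does not decide whether they take the 15-day route. It decides only whether they count as related.

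**The case against.** The strongest reply is that the article nowhere says *Not assessable* means unrelated. *Not related* is a category of its own, and the sixth category simply has no stated handling. This stands. A reader might infer a default of counting such events as not device-related, but the text supports only the narrower statement that they are not among the grades reported as related.

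A second reply is that *Possibly* already takes in the difficult cases. Its definition begins: "There is some evidence to suggest a causal relationship (e.g. the event occurred within a reasonable time after using the device", and it allows for contribution from other factors such as the patient's condition. An event shortly after device use in a severely injured patient fits this grade and is reported as related. This largely stands. A reader might infer that device harm is lost wherever device and injury cannot be separated, but the article directs most of those cases to *Possibly*. What remains for *Not assessable* is lack of information, which is narrower.

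A third reply is that safety reporting as a whole is intact. This too is mostly right. A reader might infer that such events escape expedited reporting or oversight, but the 24-hour report, sponsor reporting of unexpected serious events, recording and committee monitoring do not depend on causality. Central confirmation and incoming follow-up information also leave room to re-rate within 15 days. Room to re-rate is not a requirement to do so, however, and the non-serious events have neither safeguard.

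Finally, how safety tables display the category belongs to the analysis plan, which is not shown, so no point is made of it.

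**Conclusion.** The point holds in a limited form. Followed as written, a *Not assessable* event is outside the related group. If it is serious and unanticipated it misses the 15-day notification unless re-rated, and if it is non-serious it is not followed to resolution.

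The size cannot be given. The document states no frequency for the category, and the breadth of *Possibly* suggests that the number may be small. A reader might also infer a measurable downward bias in a count of device-related events given to the committees. The article does not say that the committees work from such a count, and it has them monitor all events.

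The primary outcome, 90-day mortality analysed by intention to treat, uses no causality rating and is unaffected. The conclusion rests on reading the three named grades as a closed list, which the repeated list in Follow-up procedures supports. This is a modest weakness in the safety rules, worth correcting because the remedy is simple.

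**What to change.** In Assessment of causality, Serious adverse event/device effect reporting and Follow-up procedures, state that events rated *Not assessable* are handled as related for reporting and follow-up until they are reclassified. Add that causality is re-rated when follow-up information arrives. This is a rule for classifying and reporting events and changes nothing in patient care.

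The cost is a few sentences in the protocol, a few more 15-day notifications and a few more non-serious events followed to resolution. Some of these will later prove unrelated and be reclassified.
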